#### 2.4.2. Logistic regression.

We determined the optimal number of time lags (1, 2, or 3) to use for logistic regression. The AUC for lag-1 was 0.73, the AUC of lag-2 was 0.78, and the AUC of lag-3 was 0.77. Hence, we selected lag-2 for regularized logistic regression. Detailed results of this analysis are included in S2 Appendix.

The best regularization scheme for logistic regression, as determined using 40-fold cross-validation within the training set, was L2 regularization with C = 0.01. In table 4, we present the model performance for regularized logistic regression, applied to the test examples.

**Table 4 pone.0289235.t004:** Prediction performance of temper outbursts for DMDD, sub-threshold DMDD, and ODD patients in held-out test examples of existing dataset, using regularized logistic regression.

	Precision	Recall	F1-score	Support
No outburst	0.97	0.82	0.89	154
Temper outburst	0.25	0.69	0.37	13

Precision, also called positive predictive value, is defined as the fraction of positive predictions that were true positives (the fraction of times where a temper outburst was endorsed out of the times that the model predicted a temper outburst). Recall, also called sensitivity, is defined as the fraction of positive examples that were predicted to be positive (the fraction of times where the model predicted a temper outburst out of the times in which a temper outburst was endorsed). F1-score is the harmonic mean of precision and recall, given by the formula F1 =  2 *  (precision *  recall)/ (precision +  recall). Support is the total number of test set observations in each category.

Table 5 presents the model weights for logistic regression, as well as Bayesian 95% credible intervals for the variables. We use the Pymc package [35] to implement the Bayesian inference, with N(0,400) prior for the intercept and N(0,0.01) prior (with sigma^2 = 0.01 chosen to match the selected hyperparameter C = 0.01) for each of the non-intercept beta coefficients. For MCMC, we used the NUTS sampler [36] with 10,000 draws and an acceptance target of 0.99.

**Table 5 pone.0289235.t005:** Model weights and intercept for L2-regularized logistic regression, and 95% credible intervals from Bayesian regression.

Variable (lag)	Coefficient	Bayesian 95% credible interval	Variable (lag)	Coefficient	Bayesian 95% credible interval
happy (1)	-0.20	[-0.26, 0.12]	happy (2)	-0.08	[-0.21, 0.18]
unhappy (1)	0.10	[-0.11, 0.27]	unhappy (2)	0.12	[-0.11, 0.27]

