#### 3.2.3. Sample size.

In the confirmatory data set (to be completed by approximately 2027), we plan to collect 20 participants, with an expected total of 300.79 prompts. We determined this prospective sample size based on a power analysis with simulated data.

We simulated data based on a simulation ground truth logistic regression model with L2 penalization, and penalization constant tuned to produce data that would result in a cross-validated accuracy of around 0.40, matching what we saw in the real data. Then, by resampling without replacement participants from the training set, and drawing labels according to the predictions of the simulation ground truth model, we produced synthetic datasets with sample sizes ranging from 1 to 34 participants. For each target sample size, we drew 1000 synthetic data sets of that size, and we assessed the power in terms of the average proportion of coefficients with incorrectly estimated signs using regularized balanced logistic regression. Detailed results are presented in S1 Appendix.

Based on the results of the power analysis, there was a consensus that, when taking into account both the clinical and methodological considerations, the more conservative would be 25 participants, even though a case could be made to justify 15 participants. Our consensus decision is to take the average of these two extremes, and therefore our new plan is to stop collecting participants for this analysis once we have collected 20 participants, which results in around 300.79 prompts on average and has a 31% average sign error for estimating coefficients (Table in S1 Appendix). For this number of prompts, assuming the same proportion of prompts will contain outbursts as in the exploratory sample (10%), we expect to see 30.08 temper outbursts on average.

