#### 3.3.3. Inference criteria.

We will compute posterior credible intervals for the precision and recall of the model [39]. Specifically, we will obtain the following statistics:

TP (number of true positives) =  True temper outburst that is predicted correctly.FP (number of false positives) =  Lack of temper outburst that is predicted as outburst.TN (number of true negatives) =  Lack of temper outburst that is predicted correctly.FN (number of false negatives) =  True temper outburst that is predicted as lack of outburst.

This allows us to perform Bayesian inference on the precision and recall as described in [32]. Using a prior lambda =  0.5 – the uninformative Jeffreys prior -- the posterior distributions of the precision and recall are as follows.

$Precision\sim Beta\left(TP+0.5.FP+0.5\right)$

$Recall\sim Beta\left(TP+0.5,FN+0.5\right)$

The posterior credible intervals can be obtained using the quantiles of these posterior distributions. Let QBeta(*q*, *a*, *b*) denote the quantile function for the Beta distribution with quantile *q* and shape parameters *a*, *b*. Hence, the 95% posterior credible interval for precision is

$Precision:\left[QBeta\left(0.025,TP+0.5.FP+0.5\right),QBeta\left(0.025,TP+0.5.FP+0.5\right)\right]$

$Recall:\left[QBeta\left(0.025,TP+0.5.FN+0.5\right),QBeta\left(0.025,TP+0.5.FN+0.5\right)\right]$

*Expected results.* Based on our preliminary results, where the regularized logistic regression model achieved a precision of 0.25 and recall of 0.69 for temper outbursts, we expect that the 95% posterior credible interval for the precision will contain a left endpoint greater than 0.1 and a right endpoint less than 0.4. We expect that the 95% posterior credible interval for recall will contain a left endpoint greater than 0.55 and a right endpoint less than 0.95.

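### The expected recall interval in section 3.3.3 does not follow from the plan's own figures: a classifier that repeats its preliminary recall would usually miss it

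*Protocol article*

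**What the plan says.** Section 3.2.3 fixes the size of the confirmatory set: "we plan to collect 20 participants, with an expected total of 300.79 prompts". At an assumed 10% outburst rate, "we expect to see 30.08 temper outbursts on average". The size was chosen on the average sign error of the coefficients (31%), not on interval width.

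Section 3.3.3 defines the inference as Jeffreys credible intervals for precision and recall. It then states expected results, which it derives from the preliminary "precision of 0.25 and recall of 0.69 for temper outbursts". For precision, it expects a left endpoint above 0.1 and a right endpoint below 0.4. For recall, it expects the "interval for recall will contain a left endpoint greater than 0.55 and a right endpoint less than 0.95".

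The preliminary figures come from Table 4 in section 2.4.2, whose rows (precision, recall, F1, support) read "No outburst 0.97 0.82 0.89 154" and "Temper outburst 0.25 0.69 0.37 13".

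**The concern.** The expected endpoints are presented as a consequence of the preliminary performance, so a classifier that performs the same way again should be likely to meet them at the planned size. For recall it is not. About 30 outbursts are too few for an interval centred near 0.69 to stay above 0.55.

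The precision expectation raises a second question. Precision depends on how common outbursts are, and the 0.25 was observed at a lower outburst rate than the one used for planning.

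The stake is how the confirmatory result will be read. Section 1.1 justifies pre-registering a trained classifier by the more specific hypotheses this allows, and these endpoints are the numerical form of that hypothesis. If they are set wrongly, a faithful replication may look like a shortfall.

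**Working it through.** **Inputs.** 300.79 prompts, a 10% outburst rate and 30.08 outbursts (section 3.2.3); recall 0.69 and precision 0.25 (section 3.3.3); supports of 13 and 154 (Table 4); prior λ = 0.5 (section 3.3.3). The printed interval formulas show the 0.025 quantile at both ends. The upper end is taken here at 0.975, as a 95% interval requires.

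**The plan's own figures.** 300.79 × 0.10 = 30.08. Table 4 is reproduced by TP 9, FN 4, FP 27, TN 127: recall 9/13 = 0.69, precision 9/36 = 0.25, no-outburst recall 127/154 = 0.82, F1 0.37. The held-out outburst rate is therefore 13/167 = 7.8%.

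**Recall at exact replication.** TP = 0.69 × 30.08 = 20.76 and FN = 9.32. Beta(21.26, 9.82) has 2.5% and 97.5% quantiles of 0.513 and 0.832. The left endpoint is below 0.55.

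**What the recall expectation requires with 30 outbursts:**

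| Detected | Interval | Expectation met? |
|---|---|---|
| 21 | 0.523 to 0.840 | no (left) |
| 22 | 0.559 to 0.865 | yes |
| 25 | 0.673 to 0.933 | yes |
| 26 | 0.713 to 0.953 | no (right) |

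So 22 to 25 detections are needed, an observed recall of at least 22/30 = 0.73. At recall 0.69, about 48 outbursts bring the left endpoint to 0.55 at the point estimate. That is not enough to meet the expectation reliably: about 90 outbursts are needed to meet it 81% of the time.

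**Precision at replication.** There are two readings of unchanged performance:
- Precision stays at 0.25. With TP 20.76 and FP 62.27, the interval is about [0.17, 0.35], inside (0.1, 0.4). At a 10% outburst rate this means the false-positive rate rises to 62.27/270.71 = 0.23.
- Sensitivity 9/13 and false-positive rate 27/154 stay fixed. At 10%, TP = 20.82 and FP = (27/154) × 270.71 = 47.46. Precision is then 20.82/68.29 = 0.305 and the interval about [0.21, 0.42], above the 0.4 limit.

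**Probability of meeting the expectations.** Simulation with 200,000 runs per row: the outburst count is binomial, TP ~ Binomial(outbursts, 9/13), FP ~ Binomial(non-outbursts, false-positive rate), and prompts are independent.

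| Prompts | Outburst rate | False-positive rate | Recall met | Precision met | Both met |
|---|---|---|---|---|---|
| 301 | 10% | 27/154 | 33% | 37% | 6% |
| 301 | 7.8% | 27/154 | 24% | 65% | 12% |
| 301 | 10% | 0.23 (precision 0.25) | 33% | 79% | 22% |
| 400 (abstract) | 10% | 27/154 | 45% | 47% | 12–13% |
| 400 (abstract) | 7.8% | 27/154 | 35% | 81% | 24% |
| 400 (abstract) | 10% | 0.23 (precision 0.25) | 45% | 91% | 38% |

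With exactly 30 outbursts, the recall expectation is met in 36–37% of studies. Adding between-participant variation (20 participants, 15 prompts each) leaves the recall figure at 32–34% at a 10% rate and 22–25% at 7.8%.

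**The case against.** The strongest reply is that nothing turns on these endpoints. They are two separate statements of what the authors expect, not a pass/fail rule, and no estimate, model, prior or sample size changes if the forecast is optimistic. Section 3.3.4 separately defines what counts as a deviation that triggers diagnostic work: an AUC difference above 0.05, an interval upper bound below the preliminary value, or an interval wider than 0.5. With sensitivity and specificity fixed at 301 prompts, the upper-bound trigger fires in about 7–8% of studies at a 7.8% outburst rate and 16% at 10%. The width trigger fires in under 0.5%. The AUC trigger cannot be simulated from the published counts.

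This stands, and it rules out two stronger readings. A reader might infer that the study has only a 6–12% chance of success. The plan states no joint criterion, and that range also requires 301 prompts and fixed sensitivity and specificity. Other readings of the protocol's own figures give 12–38%. A reader might also infer that these endpoints are the only yardstick for the result. The triggers in section 3.3.4 show otherwise.

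It also stands that the precision expectation agrees with the precision of 0.25 it is derived from. It fails at the point estimate only when the 10% rate is combined with unchanged sensitivity and specificity.

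None of this rescues the recall endpoint, which fails on the plan's own recall, outburst count and formula without any simulation.

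**Conclusion.** The expected recall left endpoint of 0.55 is wrong for the planned size. A faithful replication would meet the recall expectation in about 24–33% of studies at 301 prompts and in at most about 45% at 400. These percentages assume true recall 9/13, a binomial outburst count and independent prompts. The failure at exact replication needs none of the sampling assumptions.

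The precision expectation is sensitive to the outburst rate rather than wrong in itself. The plan takes 0.25 from a set with 7.8% outbursts and sizes the study at 10%, without saying which performance measure is expected to carry over.

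The confirmatory intervals, correctly computed, remain valid. What is affected is the pre-registered statement against which readers will compare them.

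**What to change.** Before the confirmatory data are analysed, restate the expected endpoints in section 3.3.3 for the planned size. Use one declared prompt total (301 or the abstract's 400) and one declared outburst rate, and give the probability of meeting them under replication.

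Two workable forms at 301 prompts, with sensitivity and specificity fixed:
- Lower bounds only: recall left endpoint above 0.35 and precision left endpoint above 0.10. Both are met in about 96% of studies at a 10% outburst rate and 87% at 7.8%. This form does not count better-than-expected performance as a miss.
- Two-sided limits, if the authors prefer to keep them: recall within 0.35–0.95 and precision within 0.10–0.50. Both are met in about 85% and 81% of studies respectively.

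The cost is rewording two sentences and a less favourable stated expectation. No participants are added. A change made after the data have been analysed would lose the value of pre-registration.

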#### 3.3.4. Exploratory analyses.

We include two main categories of exploratory analysis in this protocol. First is a post-hoc analysis of the performance of individualized prediction models. Second is an optional set of diagnostic analyses to be performed only if the result of the confirmatory analysis deviates from the preliminary analysis by a pre-defined margin.

##### 
Individualized prediction.

Individualized prediction involves taking the model trained on all participant data in the training set and then “fine-tuning” the model by optimizing for a few iterations on the data from an individual participant in the test set. Technically, this is accomplished by using the “warm-start” argument in the scikit-learn logistic regression class, combined with a low number of maximum iterations. The model individualized this way will then be compared to the original model in terms of performance on unseen data from that participant. This reflects a use case where an existing model would be adapted to a new participant using data collected at the beginning of a trial, and then used to generate predictions from that point onwards.

##### 
Diagnostic analyses.

There are several outcomes of the main analysis that would warrant further diagnostic analyses of the data. We are including these potential analyses in this section, since it is customary for a pre-registration to include planned exploratory analyses.

These are the scenarios which would trigger our diagnostic analyses.

1)If the AUC of the classifier on the confirmatory dataset differs from the AUC of the classifier on the preliminary dataset by more than 0.05.2)If the upper bound of the posterior credible interval for any of the following variables is less than the nominal value on the preliminary dataset. The variables are: precision for outburst, precision for non-outburst, recall for outburst, recall for non-outburst.3)If the width of the posterior credible interval for any of the variables listed in (2) above exceeds 0.5.

The diagnostic analyses include:

i)Checking for distributional shift, by comparing the means and pairwise correlations of all variables between the preliminary dataset vs the test set.ii)Checking for unusual participants, by modeling the joint distribution of the variables between participants as a mixture-of-multinomials model and looking for participants with low likelihood in the mixture-of-multinomials.iii)Checking if any of the variables included in the model are particularly to blame for poor generalization, by fitting models on the training set with one variable removed at a time and seeing if removing any of the variables this way allows for improved performance on the test set.

We believe the results of these analyses would be important in explaining any deviation from our expected results, and helpful to other researchers interested in carrying out similar experiments.

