*Temper outbursts*	Overall	Morning	Afternoon	Evening
Mean (sd) [min, max] of participant-level frequencies of temper outbursts (*n* = 54)	0.10 (0.16) [0.0, 0.73]	0.10 (0.20) [0.0, 1.0]	0.08 (0.15) [0.0, 0.5]	0.11 (0.19) [0.0, 0.67]
Mean (sd) [min, max] of participant-level frequencies of temper outbursts for male participants (*n* = 34)	0.06 (0.09) [0.0, 0.33]	0.05 (0.12) [0.0, 0.57]	0.05 (0.11) [0.0, 0.5]	0.07 (0.12) [0.0, 0.57]
Mean (sd) [min, max] of participant-level frequencies of temper outbursts for female participants (*n* = 20)	0.17 (0.21) [0.0, 0.73]	0.19 (0.27) [0.0, 1.0]	0.14 (0.18) [0.0, 0.5]	0.18 (0.24) [0.0, 0.67]

**Table 3 pone.0289235.t003:** Outcome statistics (other than temper outbursts) for participants for preliminary data included in the analysis.

Variable	n (%) for total responses (out of 932 total)				
	1 (none of the time)	2	3	4	5 (the whole time)
*Irritability and related constructs (see table 2 for temper outbursts)*					
Irritable mood	516 (55%)	212 (23%)	147 (16%)	40 (4%)	17 (2%)
Frustration	482 (52%)	169 (18%)	139 (15%)	80 (9%)	62 (7%)
*Anxiety symptoms*					
Anxious affect	738 (79%)	78 (8%)	71 (8%)	31 (3%)	14 (2%)
Momentary anxiety	764 (82%)	83 (9%)	47 (5%)	26 (3%)	12 (1%)
*Momentary feeling state*					
Tired	309 (33%)	218 (23%)	163 (17%)	126 (13%)	116 (12%)
Happy	329 (35%)	163 (17%)	156 (16%)	149 (16%)	135 (14%)
Unhappy	656 (70%)	116 (12%)	86 (9%)	37 (4%)	37 (4%)
Giddy	681 (73%)	95 (10%)	80 (9%)	48 (5%)	28 (3%)
Hungry	424 (45%)	179 (19%)	164 (18%)	91 (10%)	71 (8%)
Mood changed	480 (52%)	184 (20%)	152 (16%)	58 (6%)	58 (6%)

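### Exploratory individualized prediction (3.3.4): at the pre-fitted penalty, a warm start with few iterations does not keep the tuned model near the population model, and with an early split most youths could not be fitted

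*Protocol article*

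**What the plan says.** Section 3.3.4, under individualized prediction, takes the model trained on all training participants and optimizes it for a few iterations on one test-set participant's data. It names the tool: the warm-start argument of the scikit-learn logistic regression class, "combined with a low number of maximum iterations". The result is then "compared to the original model in terms of performance on unseen data from that participant". The stated use is to adapt an existing model with data from the start of a trial and to predict from then on.

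The only specification given for the model being adapted is in sections 2.3 and 2.4.2. It uses balanced class weights, and the chosen regularization "was L2 regularization with C = 0.01". For the Bayesian counterpart, section 2.4.2 uses an "N(0,0.01) prior (with sigma^2 = 0.01 chosen to match the selected hyperparameter C = 0.01" for each slope, so the protocol itself reads the penalty as centred on zero.

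On data per youth, section 3.2.3 says "we plan to collect 20 participants, with an expected total of 300.79 prompts" and, "assuming the same proportion of prompts will contain outbursts as in the exploratory sample (10"%), "we expect to see 30.08 temper outbursts on average". Table 2 gives the participant-level outburst frequency as mean, SD and range: "0.10 (0.16) [0.0, 0.73"]. Section 3.3.4 states no tuning window, solver, iteration count or changed penalty, and no rule for a youth without outbursts in the tuning data.

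**The concern.** The plan relies on the starting point and the iteration cap to keep the tuned model close to the population model. Neither changes what is being optimized. The objective still penalizes distance from zero, not distance from the population weights. With a strong penalty and a handful of prompts, the optimum lies near zero and can be reached in very few steps. The comparison would then set the population model against a heavily shrunken one-child model, which is not the adaptation that the section describes.

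The second difficulty is the number of outbursts. A logistic classifier in scikit-learn needs both outcome classes. A youth with no outburst in the tuning prompts gets no individualized model, and the youths who remain have been selected on the outcome. At stake is whether this exploratory analysis can say anything about adapting the shared model to a new participant.

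**Working it through.** **Plan's own figure.** 300.79 × 0.10 = 30.08 outbursts, as stated. Per youth this is 300.79 / 20 = 15.04 prompts and about 1.5 outbursts.

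**Part 1: how far the penalty moves the weights.**

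Inputs: 26 slopes and intercept −0.16 from Table 5; C = 0.01; balanced weights; predictors scaled to 0–1 (section 3.3.1). The Euclidean norm of the slopes is 0.566 and the largest absolute slope is 0.25.

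scikit-learn minimizes ½‖w‖² + C Σ sᵢ × log-lossᵢ. Setting the gradient to zero for slope j gives

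wⱼ = C [ Σ over outbursts sᵢ(1 − pᵢ)xᵢⱼ − Σ over non-outbursts sᵢpᵢxᵢⱼ ].

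With k tuning prompts, balanced weights give each class a total weight of k/2. Since x lies between 0 and 1, |wⱼ| ≤ C·k/2:

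- k = 5: at most 0.025
- k = 8: at most 0.04
- k = 10: at most 0.05

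So no slope of the converged fit can exceed 0.05, whatever the data, against slopes of up to 0.25 at the start.

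The remaining question is whether a low iteration cap stops the fit before it gets there. scikit-learn was started at the Table 5 values with C = 0.01, balanced weights and the default solver (lbfgs), on simulated tuning sets with 1–2 outbursts. Items were drawn independently from the Table 3 margins, and anger, which Table 3 omits, was given the margin of irritable mood. Labels were drawn at random.

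| Tuning prompts | Norm ratio, 2 iterations | Norm ratio, 200 iterations | Projection on population weights, 2 iterations |
|---|---|---|---|
| 5 | 0.035 | 0.032 | 0.00 |
| 8 | 0.053 | 0.050 | 0.00 |
| 10 | 0.064 | 0.059 | 0.00 |

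The fit is essentially at its optimum after two iterations. When labels followed the population score instead, the projection after two iterations was 0.01–0.03. In runs with 7 or 15 prompts, newton-cg, newton-cholesky, liblinear and sag brought the projection to about 0.01 or less after one iteration, and saga to 0.02 after two.

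Sensitivity to the penalty (lbfgs, two iterations): at C = 0.1 the projection is still about 0. At C = 1 the weights do not shrink, and the projection is 0.16–0.36.

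**Part 2: youths with no outburst in the tuning prompts.**

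Inputs: mean 0.10 and SD 0.16 (Table 2); 932 / 54 = 17.26 prompts per youth. The observed variance 0.0256 includes binomial sampling noise. Solving 0.0256 = v + (0.09 − v)/17.26 gives v = 0.0216, SD 0.147. Both SDs are carried through.

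Moment matching: a + b = 0.09/variance − 1 and a = 0.10(a + b). This gives Beta(0.316, 2.843) for SD 0.147 and Beta(0.252, 2.264) for SD 0.16. Then P(no outburst in k) = B(a, b + k)/B(a, b):

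| k | SD 0.147 | SD 0.16 |
|---|---|---|
| 5 | 71% | 72% |
| 8 | 64% | 66% |
| 10 | 60% | 63% |
| 15 | 54% | 58% |
| 21 | 49% | 54% |
| 30 | 45% | 49% |

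At k = 8 this is about 13 of 20 youths (20 × 0.64 = 12.8; 20 × 0.66 = 13.2). The minimum over all distributions on 0 to 0.8 with the stated mean and either SD is 58% at k = 7, 54% at k = 8 and 47% at k = 10.

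On single-class data every scikit-learn solver tried stopped with an error. With 7 tuning and 8 later prompts, the share with an outburst in both parts is 1 − P(7) − P(8) + P(15) = 24–25%, about 5 of 20 youths.

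**The case against.** **Keeping C = 0.01 is an inference.** The value is given for the population fit, and section 3.3.4 fixes only the warm start and the cap. This stands as a condition. Warm-starting the same estimator keeps its C, and no other value is given, but at C = 1 the weights would not shrink.

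**The split is not stated.** Section 3.3.1 says some participants complete several observation periods. This also stands: at 21 to 30 prompts the share without an outburst is about half or below.

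**Small weights need not rank prompts badly.** This stands. A reader might infer that the tuned score is unrelated to the population score. The correlation between the two was about 0.1–0.2 with independent items, but ranged from 0.43 to about 0.9 with an assumed common affect factor. The documents give no item correlations, so loss of ranking cannot be claimed.

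**Sign reversal.** A reader running the code might see reversed weights. That occurred only with lbfgs stopped at exactly one iteration. The plan names no solver and speaks of a few iterations.

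**A false conclusion about personalization.** A reader might infer that the study would wrongly report no benefit. The section sets no decision rule, each comparison is within one youth, and the single-class failure is a visible error. Selection limits the youths to whom the result applies more than it biases the paired comparison.

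**The analysis is exploratory.** It is, and the hypotheses concern a shared model. That lowers the priority. It does not make the named method do what the section describes.

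**Conclusion.** The concern holds conditionally and for the exploratory analysis only. If the refit keeps L2 with C = 0.01 and balanced weights, a low iteration cap does not hold the tuned model near the population model. With 5–10 prompts, roughly 5% of the weight norm remains after about two iterations, with almost no projection on the population weights. The bound on the converged slopes does not depend on simulated data. The figures after two iterations do use simulated predictors.

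If tuning uses about the first 5–10 prompts of one 7-day period, about 60–72% of youths are expected to give no fit. This assumes that the confirmatory youths resemble those in Table 2 and that a beta-binomial describes them. At 8 prompts the share exceeds half for any distribution with that mean and SD. At 10 prompts it need not.

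The planned confirmatory precision and recall are not affected. The change is worth making before the confirmatory data are analysed, but it is not critical.

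**What to change.** Replace the warm-start refit in section 3.3.4 with an update centred on the frozen model. Either of these would do:

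- enter the frozen linear predictor as an offset and estimate a child-specific intercept with a Gaussian prior; or
- estimate all weights with a Gaussian prior centred on the frozen Table 5 weights, with a prior on the intercept too.

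Both are defined when the tuning data hold one class. Balanced weights cannot be recomputed from one-class data, so fix the class weights at their training-set values. The Table 5 note shows that the frozen intercept depends on that weighting.

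State one tuning window that applies to every youth, including those with several observation periods. Keep all 20 youths, and compare adapted with original predictions on all later prompts, pooled. A resampling interval by participant would suit the clustering.

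If the authors prefer to keep the warm start, they should at least state C, the solver, the iteration count, the split and a rule for one-class tuning data. That makes the analysis reproducible, but at C = 0.01 it does not cure the shrinkage.

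Cost: a reworded paragraph, a few lines of code and slightly more analysis work. No new data are needed.

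### The expected precision range in 3.3.3 and the precision references in trigger 2 come from a test set with 7.8% outbursts, but the confirmatory set is planned at 10%

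*Protocol article*

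**What the plan says.** Table 4 in section 2.4.2 gives the preliminary test-set performance. Its rows, in the order precision, recall, F1 and support, are "No outburst 0.97 0.82 0.89 154" and "Temper outburst 0.25 0.69 0.37 13". The note explains that "Support is the total number of test set observations in each category", so the test set held 13 outbursts in 13 + 154 = 167 prompts.

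Section 3.2.3 sizes the confirmatory set: "we plan to collect 20 participants, with an expected total of 300.79 prompts". It assumes that 10% of prompts contain an outburst, as in the exploratory sample, and concludes "we expect to see 30.08 temper outbursts on average". The abstract gives an expected total of 400 time points instead.

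Section 3.3.3 takes its expected results from the preliminary findings, "where the regularized logistic regression model achieved a precision of 0.25 and recall of 0.69 for temper outbursts". It expects the 95% interval for precision to have a left endpoint above 0.1 and a right endpoint below 0.4.

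Section 3.3.4 lists three scenarios that start the diagnostic analyses. The second applies if the upper bound of the credible interval for any of four quantities "is less than the nominal value on the preliminary dataset". The four are precision and recall for outburst and for non-outburst.

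**The concern.** Precision for outburst and precision for non-outburst are predictive values. They move with the share of prompts that contain an outburst even if the classifier separates the two kinds of prompt exactly as before. The two recalls do not move in this way.

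The plan uses two different proportions without linking them: 7.8% behind the precision benchmarks and 10% in the sample-size section. The confirmatory study tests a classifier that is already fitted and will not be refitted, and precision is one of its two reported measures. If the benchmark belongs to a different outburst proportion, a result on either side of it is hard to read: the classifier may have changed, or only the mix of prompts.

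**Working it through.** **Inputs.** Table 4 (2.4.2); 300.79 prompts and 10% outbursts (3.2.3); 400 time points (abstract); Jeffreys Beta intervals with 0.5 added to each count (3.3.3). The printed interval formulas show the 0.025 quantile at both ends. I used 0.975 for the upper end, which is the evident intent of a 95% interval.

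**Step 1: reproduce Table 4.** Of all integer tables with 13 outbursts and 154 non-outbursts, only one returns every rounded entry: TP 9, FN 4, FP 27, TN 127.
- Outburst precision 9/36 = 0.250; recall 9/13 = 0.692.
- Non-outburst precision 127/131 = 0.9695; recall 127/154 = 0.825.
- Outburst proportion 13/167 = 7.8%.
- The planned count also reproduces: 300.79 × 0.10 = 30.08.

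**Step 2: move to 10% with both recalls fixed.**
- Outburst precision = 0.10 × 0.6923 / (0.10 × 0.6923 + 0.90 × 0.1753) = 0.0692 / (0.0692 + 0.1578) = 0.305.
- Non-outburst precision = 0.90 × 0.8247 / (0.90 × 0.8247 + 0.10 × 0.3077) = 0.7422 / (0.7422 + 0.0308) = 0.960.

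**Step 3: intervals for outburst precision at expected counts.**

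| Prompts | Outbursts | Precision | 95% interval |
|---|---|---|---|
| 300.79 | 7.8% | 0.250 | 0.157 to 0.365 |
| 300.79 | 10% | 0.305 | 0.206 to 0.420 |
| 400 | 10% | 0.305 | 0.217 to 0.405 |

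At 7.8% the interval lies inside the stated range. At 10% its right endpoint passes 0.4 for either prompt total. For non-outburst precision at 300.79 prompts and 10%, the upper bound is 0.980, so that component does not fire at expected counts. Its excess firing is a matter of frequency.

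**Step 4: simulation for an unchanged classifier.** 301 prompts, binomial outburst count, prompts independent, both recalls as in Table 4, reference values unrounded.

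| Event | At 7.8% | At 10% |
|---|---|---|
| Precision interval wholly within the stated range | 65% | 37% |
| Right endpoint below 0.4 | 74% | 38% |
| Non-outburst precision component fires | 3% | 13% |
| Outburst precision component fires | 2.5% | 0.2% |
| Trigger 2 fires (any of four) | 8% | 16% |

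With 400 prompts at 10%, the range is met in 47% of sets. With the reference values matched to 10% (0.305 and 0.960), the non-outburst precision component returns to about 3%.

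**Step 5: sensitivity.** With the outburst count fixed at 30 of 301, the range is met in 33% of sets and the non-outburst precision component fires in about 10%. With outbursts clustered within participants (assumed intraclass correlation 0.1 to 0.2) at 10%, the range is met in 35 to 38%, and that component fires in 18 to 21%, against 6 to 8% at 7.8%.

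**Step 6: a classifier that has really deteriorated.** Assume recall 0.60 and non-outburst recall 0.70 at 301 prompts. The outburst precision component fires in 74% of sets at 7.8% but only 36% at 10%; against the matched 0.305 it fires in 81%. Trigger 2 as a whole still fires in about 99.9% of sets at both proportions, because the non-outburst recall component alone fires in about 99.8%.

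**The case against.** **Is deterioration missed?** A reader might infer from Step 6 that the fixed 0.25 lets real deterioration through. The documents do not support that. Trigger 2 needs only one of four quantities to cross, and in the case examined non-outburst recall crosses almost every time. Only the outburst precision component is blunted.

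**Does the plan read a shift in outburst rate as a failed classifier?** Not in its text. The trigger opens an optional set of exploratory diagnostics, and the first of them compares the means of all variables between the datasets, which could show a changed outburst rate. Diagnostics can also start under trigger 1, an AUC difference above 0.05. Under an assumed binormal score model matched to Table 4's recalls, triggers 1 and 2 together fire in about 27% of sets at 7.8% and about 29% at 10%. The mismatch then adds little to the chance that diagnostics run. That model is only illustrative: it implies an AUC of 0.845, whereas 2.4.2 reports 0.78.

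**Is the expected range a success criterion?** No. Section 3.3.3 attaches no decision to it, and the miss is towards higher precision. The range is already missed in about 35% of sets at 7.8%, so it is tight at this sample size for a separate reason.

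**Are the inputs firm?** No. The Jeffreys interval for 13/167 is 4.4% to 12.6%, which contains 10%, and that for recall 9/13 is 0.42 to 0.89. Since mood items and sex are predictors, a sample with more outbursts could also have a different false-positive rate.

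These points limit the consequences. They do not remove the inconsistency between the 10% used for planning and the 7.8% behind the precision benchmarks.

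**Conclusion.** The point holds as a minor correction. On the plan's own figures, 10% outbursts with unchanged recalls implies a precision of about 0.305 rather than 0.25, with an expected interval that passes the stated upper limit of 0.4. An unchanged classifier is more likely to miss the stated range than to meet it: 37% met at 301 prompts and 47% at 400, against 65% at 301 prompts and 7.8%. In trigger 2, the non-outburst precision component fires in about 13% of sets instead of 3%, and the whole trigger in about 16% instead of 8%.

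The percentages rest on constant Table 4 recalls, independent prompts and a 0.975 upper quantile. The direction holds with 400 prompts, a fixed outburst count and clustering. The planned estimates of precision and recall, and their intervals, are not affected. What needs correcting is the benchmarks against which they will be read.

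**What to change.** - **Section 3.3.3.** Restate the expected precision as about 0.30 at 10% outbursts, with an expected 95% interval of about 0.21 to 0.42 at 301 prompts. Say that this depends on the outburst proportion and on Table 4 recalls that are imprecise (13 outbursts). Present it as the interval at expected counts, not as limits that the endpoints must fall within.
- **Section 3.3.4, trigger 2.** Compare the two precisions with the values that Table 4's recalls (9/13 and 127/154) imply at the outburst proportion observed in the confirmatory set, about 0.305 and 0.960 at 10%. Alternatively, limit trigger 2 to the two recalls.

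The cost is wording and one line of arithmetic, with no new data. The small downside of the matched references is that they are known only once the confirmatory outburst proportion is known. The formula can be fixed in advance.
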